#### 20.11b Program completion

We will use a logistic multivariate regression analysis to model program completion where the observation for program completion will be coded as binary: completion (=1) and drop-out (=0). The interventions (Distress thermometer and MH&A) will be included as well as a variable for their interaction effect. We will also include time period (year-quarter) and an interaction term between the time period and each intervention (Distress thermometer and MH&A). Clustered robust standard errors will be used to account for cohort intra-cluster correlation. Post-regression analyses using *margins* command will be used to estimate difference in program completion between treatment groups.

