## 14.1 Difference in proportion of AFDs

The sample size is fixed at approximately 448 individuals. We anticipate that the first few cohorts will be asked to pilot the screening tool, potentially removing up to 50 apprentices from the final sample size. We will use a fixed sample size of 400 apprentices, divided equally between Sudbury and Barrie sites. The expected cohort sizes will range from 6 to 10 apprentices, resulting in 20 to 34 cohorts per site. We will use a 3-level hierarchical design to model differences in proportion of AFDs where the daily attendance (Level 1) will be coded as binary; 0 for absence and 1 for attendance. Level 1 observations are clustered within individual apprentices (Level 2), which are nested within individual cohorts (Level 3). The sites (Sudbury and Barrie) and start date of cohort enrollment (q1 (January-March); q2 (April-June); q3 (July-Sept); q4 (Oct-Dec) and year) will be included as confounding variables in Level 1 and will not enter into the power calculations. Using this design, we performed a sensitivity analysis to determine the power to observe different primary outcome effect sizes with an $\alpha$-level 0.05**.**  As can be seen in the following table, even small differences in attendance (5% difference in proportions of AFDs) would still be detected with power ≥ 80% as long as the Level 2 inter-cluster correlation ≤ 0.125, a very reasonable assumption as there is no reason to believe that these apprentices’ attendance behaviours will be highly correlated with each other (23).

|  | **Scenarios**^1^ | | | | | | | |
| --- | --- | --- | --- | --- | --- | --- | --- | --- |
| **Variables** | 1 | 2 | 3 | 4 | 5 | 6 | 7 | 8 |
| Test Significance Level, α​ | 0.05 | 0.05 | 0.05 | 0.05 | 0.05 | 0.05 | 0.05 | 0.05 |
| Mean Difference, δ = µ₁ - µ₂​ | 0.1 | 0.15 | 0.05 | 0.05 | 0.05 | 0.05 | 0.05 | 0.1 |
| Standard Deviation, σ​ | 0.1 | 0.1 | 0.1 | 0.1 | 0.1 | 0.1 | 0.15 | 0.15 |
| Level 1 Unit Correlation, ρ₁​ | 0.75 | 0.75 | 0.75 | 0.75 | 0.75 | 0.75 | 0.75 | 0.75 |
| Level 2 Unit Correlation, ρ₂​ | 0.5 | 0.5 | 0.5 | 0.25 | 0.125 | 0.05 | 0.05 | 0.05 |
| Number of Level 3 Units in Group 1, C₁​ | 15 | 15 | 15 | 15 | 15 | 15 | 15 | 15 |
| Number of Level 3 Units in Group 2, C₂​ | 15 | 15 | 15 | 15 | 15 | 15 | 15 | 15 |
| Level 3 Units per Group Ratio, C₂/C₁​ | 1 | 1 | 1 | 1 | 1 | 1 | 1 | 1 |
| Number of Level 2 Units per Level 3 Unit, K​ | 6 | 6 | 6 | 6 | 6 | 6 | 6 | 6 |

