## 14.2 Difference in proportions of TDTP completion

Historical cohorts have demonstrated variation in program completion proportions but have been generally observed at a 75-80% graduation / completion rate. In this cluster randomized trial comparing the difference in proportions of TDTP completion, we define an *a priori* difference of ≥ 0.1 in completion proportions as the lower limit of a minimally significant difference (24). This is opinion-based on an informal survey of TDTP stakeholders. Given the same fixed sample and cohort size estimates discussed in Section 14.1, we performed a sensitivity analysis to determine the power to observe a difference in program completion proportions ≥ 0.1 using different control group completion rates with an $\alpha$-level 0.05**.**  As can be seen in the following table, a difference in completion proportions of 0.1 would be detected with power ≥ 80% as long as the control group completion proportion was ≥ 0.8, a reasonable assumption given the historically observed program completion proportions.

|  | **Scenarios**^1^ | | | | | | |
| --- | --- | --- | --- | --- | --- | --- | --- |
| **Variables** | 1 | 2 | 3 | 4 | 5 | 6 | 7 |
| Test Significance Level, α​ | 0.05 | 0.05 | 0.05 | 0.05 | 0.05 | 0.05 | 0.05 |
| 1 or 2-Sided Test?​ | Two | Two | Two | Two | Two | Two | Two |
| Control Group Proportion (p2)​ | 0.75 | 0.75 | 0.75 | 0.75 | 0.8 | 0.8 | 0.8 |
| Test Statistic under H0​ | 0 | 0 | 0 | 0 | 0 | 0 | 0 |
| Test Statistic under H1​ | 0.1 | 0.1 | 0.1 | 0.1 | 0.1 | 0.1 | 0.1 |
| Intracluster Correlation (ICC)​ | 0 | 0.05 | 0 | 0 | 0 | 0 | 0 |
| Clusters in Treatment Group (K1)​ | 20 | 20 | 33 | 25 | 20 | 33 | 25 |
| Clusters in Control Group (K2)​ | 20 | 20 | 33 | 25 | 20 | 33 | 25 |
| Cluster Ratio (K2/K1)​ | 1 | 1 | 1 | 1 | 1 | 1 | 1 |
| Cluster Sample Size in Treatment Group (M1)​ | 10 | 10 | 6 | 8 | 10 | 6 | 8 |
| Cluster Sample Size in Control Group (M2)​ | 10 | 10 | 6 | 8 | 10 | 6 | 8 |
| Cluster Sample Size Ratio (M2/M1)​ | 1 | 1 | 1 | 1 | 1 | 1 | 1 |
| Power (%)​ | 70.6 | 54.6 | 70.2 | 70.6 | 80.2 | 79.8 | 80.2 |

^1^ Highlighted cells (Yellow) represent changes from previous scenario

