### 18.13 Study-specific data

| Data | Description | Data type |
| --- | --- | --- |
| **Cluster criteria** |  |  |
| City | Barrie vs Sudbury | Categorical |
| Enrollment | Quarter-year  Quarter (Q):  Q1=January 1 – March 31  Q2=April 1 – June 30  Q3=July 1 – September 30  Q4=October 1 – December 31 | Categorical |
| **Primary Outcomes** |  |  |
| Program completion | Yes | Categorical |
|  | No |  |
| Employment (full-time at 24 months) |  | Categorical |
| Self-report | Yes | Categorical |
|  | Employer verified |  |
|  | Employer not verified |  |
|  | No |  |
| **Secondary Outcomes** |  |  |
| Date/Time |  | Continuous |
| Mental health consult | ddmmyy:hh |  |
| Addictions consult |  |  |
| TDTP Satisfaction Survey | National Centre for Vocational Education Research Student Outcomes Survey (21) | Categorical |
| Distress Thermometer |  |  |
| Acceptability survey | Section 12.25 | Categorical |
| Feasibility survey | Section 12.26 | Categorical |

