### 20.11 Primary

#### 20.11a Program attendance

We will use a 3-level hierarchical design to model the program attendance data where the observation for each day (Level 1) will be coded as binary; attendance (=1) versus absence (=0). Level 1 observations are clustered within individual apprentices (Level 2) , which are nested within cohorts (Level 3). We will analyse the outcome data using multi-level, mixed-effects logistic regression analysis with fixed effects estimated for the variance in the intercepts of both apprentice and cohort levels. The interventions (Distress thermometer and MH&A) will be included as well as a variable for their interaction effect. We will also include time period (year-quarter) and an interaction term between the time period and each intervention (Distress thermometer and MH&A). A sensitivity analysis will be conducted to compare this baseline model with an extended model that includes any baseline demographic or clinical variables that appear to be unbalanced at Level 1. The models will be compared using the likelihood-ratio comparison test for superiority. Post-regression analyses using *margins* command will be used to estimate difference in program attendance between treatment groups.

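### The primary completion model, and by form the employment model, crosses categorical year-quarter with both interventions, which is too many cohort-level parameters for 40 to 68 cohorts and inflates type I error

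*Protocol*

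**What the plan says.** Section 20.11b prescribes a logistic model for completion. On the treatment terms it says: "The interventions (Distress thermometer and MH&A) will be included as well as a variable for their interaction effect". On time it says: "We will also include time period (year-quarter) and an interaction term between the time period and each intervention (Distress thermometer and MH&A". Standard errors are to be robust to clustering by cohort, and the *margins* command supplies the between-group difference. Section 20.11c repeats this for full-time employment. Section 20.11a puts the same fixed terms into a mixed-effects logistic model for daily attendance, described as "with fixed effects estimated for the variance in the intercepts of both apprentice and cohort levels".

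Section 18.13 lists the enrolment quarter-year as a categorical variable with calendar-quarter levels ("Q1=January 1 – March 31" and so on). On size, Section 14.1 says "We will use a fixed sample size of 400 apprentices, divided equally between Sudbury and Barrie sites" and "The expected cohort sizes will range from 6 to 10 apprentices, resulting in 20 to 34 cohorts per site". Section 14.2 says that historical completion proportions "have been generally observed at a 75-80% graduation / completion rate". Section 8 makes the MH&A service available only in Barrie, so MH&A and site are the same variable.

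**The concern.** The tool is allocated by cohort, MH&A is fixed by site, and each cohort has one start quarter. Every treatment and time term in the model is therefore constant within a cohort, so its information comes from the number of cohorts, not from the 400 apprentices. Two sets of quarter-by-intervention terms use up most of that information when accrual is long. One set is only quarter by site.

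An uncorrected cohort-robust variance is then too small, because the model fits the few cohorts in each quarter too closely. When a quarter lacks one arm or one site, or has no drop-outs in a cell, some terms cannot be estimated. The contrast then depends on what the software drops. At stake are the confidence interval and the error rate of a primary comparison.

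**Working it through.** **1. The plan's own figures.** Section 14.2 reports power for a plain two-group comparison. With δ = 0.10, n per group divided by 1 + (m − 1)·ICC, and two-sided α = 0.05:

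power = Φ{[δ√n − 1.96·√(2p̄q̄)] / √(p₁q₁ + p₂q₂)}

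- Control 0.75, n = 200: (1.414 − 1.109)/0.561 = 0.544, power 70.7% (stated 70.6).
- Control 0.75, ICC 0.05, m = 10: n = 200/1.45 = 137.9, power 54.7% (stated 54.6).
- Control 0.80, n = 200: (1.414 − 0.990)/0.5 = 0.849, power 80.2% (stated 80.2).

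The other scenarios agree within 0.1 point. These figures contain no time terms. Section 14.1 says that site and start quarter are left out of the power calculations.

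**2. Parameter count.** Cohorts: 200/10 = 20 to 200/6 ≈ 34 per site, so 40 to 68 in all. Drop-outs at 75–80% completion: 80 to 100 among 400. Parameters: 4 (intercept, tool, MH&A, tool × MH&A) plus 3(Q − 1) (quarter, quarter × tool, quarter × MH&A).

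| Quarters | Parameters | Cohorts minus parameters | Drop-outs per parameter |
|---|---|---|---|
| 4 | 13 | 27–55 | 6.2–7.7 |
| 8 | 25 | 15–43 | 3.2–4.0 |
| 12 | 37 | 3–31 | 2.2–2.7 |

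With 40 cohorts over 8 quarters there are 5 cohorts per quarter, about 2.5 per tool arm.

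**3. Number of quarters (assumption).** The protocol gives no accrual length, and the date of first enrolment is still open. The budget (Section 34) gives two indirect hints. First, 24 tablets for 200 tool apprentices means 200/24 ≈ 8.3 rounds of 12 weeks, or about 2 years (8 quarters). Second, 90 audit hours at 15 per 6 months is 3 years. That is 12 quarters if all of it is accrual, or about 4 if it includes the 24-month employment follow-up. Hence the range 4 to 12.

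**4. Simulated type I error, completion model of 20.11b.** No tool effect; blocks of 4 within site; cohorts spread evenly over fully crossed quarters; cohort sandwich variance with G/(G − 1); z-test at 5%.

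Margins difference at completion 0.80, ICC 0.05, 400 runs per setting, with (without) the time-by-intervention terms:

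| Layout per site | Q = 4 | Q = 6 | Q = 8 | Q = 12 |
|---|---|---|---|---|
| 20 cohorts of 10 | 13% (7.5%) | 24% (8.5%) | 43% (8%) | not run |
| 33 cohorts of 6 | 8% (6%) | 14% (8%) | 18% (7%) | 39% (9%) |

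A wider grid used completion 0.75 and 0.80, ICC 0 and 0.05, 40, 50 or 68 cohorts, three tests (tool coefficient, tool × MH&A, margins difference) and 1,000 runs. Perfectly predicted observations were dropped and the model refitted. It gave 7–17% at Q = 4, 11–36% at Q = 8 and 20–56% at Q = 12. Without the interactions, at completion 0.75, it gave about 6–9%, 6–12% and 8–14%. With no time terms at all the error was about 5–7%. Drawing start quarters at random at Q = 12 gave 38–40% with 40 cohorts and 19–21% with 68 (coefficient and margins tests).

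The cause is visible at Q = 8 with 40 cohorts: the empirical SD of the estimate is 0.068 and the mean reported standard error 0.027. The design matrix is rank-deficient in 47% of those runs.

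**5. Separation in the wider grid.** Under 1% at Q = 4, 9–67% at Q = 8, 62–98% at Q = 12. Non-estimable terms occur in 1–50% of runs at Q = 8 and 39–100% at Q = 12.

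**6. Additive coding.** If quarter and year enter as separate factors, the model has 4 + 3(3 + 1) = 16 parameters over two years and 4 + 3(3 + 2) = 19 over three. Type I error is then 18% and 23% with 20 cohorts per site, and 9.5% and 9% with 33. Separation is at most 4.5%.

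**7. Attendance.** A balanced linear mixed-model analogue (maximum likelihood, z-test) gives about 5% at cohort ICC 0 and 8–12% at 0.05. It reaches 32% only at ICC 0.25 with 40 cohorts and 12 quarters.

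**The case against.** The best defence is that any single error rate is conditional. Accrual length is unstated and the budget hints conflict. A reader might take 41–43% as the plan's error rate, but that is one cell: 8 quarters, 40 cohorts, full crossing. It is neither a document figure nor the maximum. At 4 quarters the excess is modest and separation is rare, so a general statement that the model separates would be wrong. Section 14.1 names the quarter and the year, which can be read as additive coding, and that reduces the inflation. All of this stands, and it is why ranges are given.

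The figures also do not carry over to every primary model. Attendance names no cluster-robust standard errors. Employment is analysed among graduates only (Section 12.13), no employment rate is stated, and it was not simulated.

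A reader might further infer from the words "with fixed effects estimated for the variance in the intercepts of both apprentice and cohort levels" that cohort dummies would absorb the tool effect. The text does not support that. The same sentence specifies a multi-level mixed-effects model and estimates intercept variances, which is a random-intercept model. It is a slip of wording.

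Finally, a small-sample correction is often left to the SAP, so its absence alone is no defect. The crossed time terms, however, are fixed in the protocol, and they inflate the error under either coding.

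**Conclusion.** The point holds for completion and, by its identical form, applies to employment without a simulated size. As written, the completion model is over-parameterised for 40 to 68 cohorts, and type I error exceeded 5% in every completion scenario run. With fully crossed quarters and completion of 0.75–0.80 it is about 7–17% at 4 quarters, 11–43% at 8 and 20% or more at 12, against about 6–14% without the interactions. With additive coding over two or three years it is about 9–23%. Separation is rare at 4 quarters; rank deficiency or separation is common from about 8 quarters when cohorts are few. Attendance shares the over-parameterisation with milder inflation, about 5–12% at cohort ICC up to 0.05. The size rests on the assumed 4 to 12 quarters, ICC of 0 to 0.05, and an uncorrected sandwich with a z reference.

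**What to change.** - In Sections 20.11a to 20.11c, delete the time-period-by-intervention terms from the primary models.
- Keep the tool, MH&A (site), their interaction, and calendar time as a main effect with few degrees of freedom, for example linear or half-year.
- Show time by tool only as an exploratory analysis.
- For completion and employment, use small-sample corrected cohort-robust standard errors with t degrees of freedom based on cohorts. Deletion alone leaves about 6–14%, so the correction is needed as well.
- As a wording correction only, let 20.11a and 20.12a say random intercepts for apprentice and cohort.

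The cost is a few sentences in Section 20. The downside is that drift in the tool effect over time is examined only as an exploratory question.

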**Figure 1: 2x2 factorial design for case management strategies**

|  | Self-report tool for distress | |
| --- | --- | --- |
| MH&A Service | Control | Intervention |
| Control (Sudbury) | BCM | ICM^10^ |
| Intervention (Barrie) | ICM^01^ | ICM^11^ |

In this 2x2 factorial design, the intervention effects for 3 ICM models will be estimated. For the cohorts located in Sudbury, the current standard of case management will be the BCM model. The reason for this is the absence of a working relationship between Community Builders® and the MH&A program at Health Sciences North, the healthcare authority for the greater Sudbury region, that would permit the establishment of a similar fit for purpose service as the one created for the Barrie cohort. In this BCM model, the Training Program Coordinator in Sudbury will host bi-weekly meetings with each apprentice to ensure that all boundaries to skilled trades employment are eliminated. This includes, but is not limited to, check-ins (frequency) with the apprentice through Slack, frequent visits to the construction sites, and monitoring of the feedback forms that mentors complete weekly on the attendance, attitude, and coachability of their apprentice. For the ICM^10^ and ICM^01^ models, this BCM model will serve as the control for estimating the effects of the self-report for distress tool and the MH&A program, respectively. For the ICM^11^ model, both the ICM^10^ and the ICM^01^ models will serve as the controls to estimate the interaction effect for the combined self-report for distress tool and the MH&A program.

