# 7 Objectives

## 7.1 Primary

1) To compare the effect of ICM^10^ and ICM^01^ versus BCM on reducing absenteeism in apprentices enrolled in TDTP

2) To compare the effect of ICM^10^ and ICM^01^ versus BCM on reducing drop-out rates in apprentices enrolled in TDTP

3) To compare the effect of ICM^10^ and ICM^01^ versus BCM on reducing unemployment rates in apprentices enrolled in TDTP

4) To compare the effect of ICM^11^ versus ICM^10^ and ICM^01^ on reducing absenteeism in apprentices enrolled in TDTP

5) To compare the effect of ICM^11^ versus ICM^10^ and ICM^01^ on reducing drop-out rates in apprentices enrolled in TDTP

6) To compare the effect of ICM^11^ versus ICM^10^ and ICM^01^ on reducing unemployment rates in apprentices enrolled in TDTP

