# 8 Design

The *TeachMeToBuild* trial is designed as a pragmatic, open-label, 2x2 factorial, cluster randomized, controlled, superiority study. Each cohort (cluster) will be randomized in a 1:1 allocation ratio to the self-report tool for distress using a stratified, permuted-block group schema according to the following strata:

1) Study site (Sudbury, Barrie)

The MH&A fit-for-purpose service will only be available to apprentices located at the Barrie site.

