# 20 Statistical methods

## 20.1 Outcomes

The intervention arms (ICM^10^ (Distress Thermometer screening tool), ICM^01^ (MH&A fit-for-purpose program), ICM^11^ (Both Distress Thermometer and MH&A) will be compared against the active comparator (BCM) for all primary and secondary analyses where applicable. All inferential and descriptive analyses will be at the individual level after accounting for the effects of clustering (id and cohort).

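### Completion and employment use cohort-robust standard errors with no small-sample correction named, while the ICM10 versus BCM contrast rests on only 10 to 17 Sudbury cohorts per arm

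*Protocol*

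**What the plan says.** Sections 20.11b and 20.11c both prescribe logistic regression with terms for the tool, the MH&A service, their interaction, year-quarter, and year-quarter by each intervention, followed by the margins command. On clustering both say: "Clustered robust standard errors will be used to account for cohort intra-cluster correlation". Neither names a finite-sample adjustment or a reference distribution.

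Section 20.1 says that the three ICM arms "will be compared against the active comparator (BCM) for all primary and secondary analyses where applicable". Section 7.1 lists as a primary objective: "To compare the effect of ICM^10^ and ICM^01^ versus BCM on reducing drop-out rates in apprentices enrolled in TDTP". In Figure 1 both arms of the tool comparison without the MH&A service lie in one city: "Control (Sudbury) | BCM | ICM^10".

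Section 8 randomises within site: "Each cohort (cluster) will be randomized in a 1:1 allocation ratio to the self-report tool for distress". Section 14.1 gives the numbers: "We will use a fixed sample size of 400 apprentices, divided equally between Sudbury and Barrie sites" and "The expected cohort sizes will range from 6 to 10 apprentices, resulting in 20 to 34 cohorts per site".

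**The concern.** The ordinary cluster-robust (sandwich) variance is a large-sample device, and what counts is the number of clusters behind the contrast, not the number of participants. The model contains the tool by MH&A interaction, so ICM10 versus BCM is a within-Sudbury comparison. The residuals of each arm are taken about that arm's own fitted rate, which makes the variance estimate too small by roughly one part in K, where K is the number of cohorts per arm. A default multiplier based on all cohorts at both sites hardly repairs this. A normal reference also ignores how uncertain the variance estimate is.

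If the method is run at its default, intervals for two of the three primary outcomes are too narrow, and the stated 5% error rate is exceeded before any question of multiplicity. This matters most for ICM10 versus BCM, because it is the only comparison with BCM in which allocation is randomised: Section 8 ties the MH&A service to the Barrie site.

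**Working it through.** **The plan's own figures.** The protocol states no achieved type I error, only a nominal two-sided 0.05 (14.2). Its completion power table can be reproduced with n = KM/(1 + (M-1)ICC) per group and a pooled-variance test of two proportions. Scenario 2, for example, gives n = 200/1.45 = 137.9. The results are 70.7, 54.7, 70.3, 70.7, 80.2, 79.8 and 80.2%, against the stated 70.6, 54.6, 70.2, 70.6, 80.2, 79.8 and 80.2%. The table assumes an exact 0.05 and 20 to 33 clusters per group. That matches a site total, or the tool effect pooled over sites, but not ICM10 versus BCM.

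**Cohorts behind the contrast.** "resulting in 20 to 34 cohorts per site", split 1:1 within site, gives 20/2 = 10 to 34/2 = 17 per arm. Over both sites, G = 4K = 40 to 68.

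**Approximation by hand (risk difference, equal cohorts, no quarter terms).** The model then has one parameter per cell. The sandwich variance of a cell proportion is the sum of (y_j - m p̂)² over cohorts, divided by (Km)². Its expectation is (1 - 1/K) times the true variance. The default multiplies it by G/(G-1).
- K = 10: variance ratio 0.900 × 40/39 = 0.923; standard error ratio 0.961; effective cut-off 1.960 × 0.961 = 1.883. On 2K-2 = 18 degrees of freedom the two-sided tail is 7.6%.
- K = 17: 0.941 × 68/67 = 0.955; standard error ratio 0.977; cut-off 1.916. On 32 degrees of freedom the tail is 6.4%.

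**Simulation (60,000 null trials per setting, beta-binomial cohorts, rates 0.75-0.9, ICC 0-0.1, no quarter terms, G/(G-1) with a normal reference).**

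| Cohorts per arm × size | Risk difference | Logit |
|---|---|---|
| 10 × 10 | 7.2-7.7% | 6.7-8.0% |
| 17 × 6 | 6.2-6.5% | 5.4-6.4% |

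Repeat runs agree to within a few tenths of a point. At 10 cohorts of 10 the lowest logit figure in any run was 6.3%. The rates are inflated at ICC = 0 as well, so the near-zero ICCs in 14.2 do not remove the problem.

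**Tool effect pooled over sites, same model.** The bias per cell is unchanged but the degrees of freedom are 4K-4. The tail beyond 1.883 on 36 degrees of freedom is 6.8%, and beyond 1.916 on 64 it is 6.0%. Simulation gives about 6.6-6.9% and 5.8-6.1%. If the pooled effect is treated instead as a simple two-group comparison of 20 versus 20 to 34 versus 34 cohorts, the rate is 5.3-6.4%.

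**Employment.** The protocol gives no employment rate, and the denominator is graduates (12.13). Assuming that 78% graduate and that 50-75% of graduates are employed, the risk-difference test runs at 7.6-8.2% with 10 cohorts per arm and 6.4-6.8% with 17. These ranges include the sandwich without any multiplier.

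**After correction (arm-level K/(K-1), t on 2K-2 degrees of freedom, no quarter terms).** The completion test returns to about 4.4-5.1% on the risk difference and about 4.0-5.1% on the logit. A t reference on G-1 degrees of freedom alone is not enough: it leaves 5.7-6.9%.

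**The case against.** The strongest objection is that the protocol is silent rather than wrong. CR2, or a K/(K-1) factor with t degrees of freedom, is itself a clustered robust standard error and fits the quoted sentence. The choice of correction and reference distribution can properly be left to a SAP, which is not shown here. This stands to the extent that a reader might infer that the protocol commits to uncorrected errors or rules out an adjustment; it does neither. But the stated method, carried out with its usual default, does not hold its level for a primary contrast, so the choice should be fixed explicitly.

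The second objection is size: the excess is about 0.5 to 3 points and nearly vanishes on the logit scale with 17 cohorts per arm. That is right.

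Third, the check leaves out the quarter terms that are in the planned model. It does so to isolate this mechanism. Linear-probability runs gave 8-15% at 4 quarters and 16-36% at 8 quarters with the interactions in, some fits being rank-deficient. A reader might be tempted to quote those as the size of this problem. They belong to a separate problem, the number of quarter terms, and depend on a number of quarters that the protocol does not give. For the same reason the recovery to about 5% is shown only for the model without those terms.

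Fourth, a rate near 9% appears if every cohort has 15 members (7 per arm). That takes the top of the class size in 5.15, whereas the sample-size section plans 6 to 10, so it is not the planned case.

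**Conclusion.** The point holds as a modest small-sample defect in how the method is fixed. Run at its usual default without quarter terms, the nominal 5% test of ICM10 versus BCM on completion has a true size of about 6.7-8.0% at 10 cohorts of 10 per arm (6.3% at the lowest in repeat runs) and about 5.4-6.5% at 17 of 6. The quarter terms can only add to this.

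The conclusion assumes that the software default applies, that cohorts number 20 to 34 per site, that completion is 0.75-0.9, and that the ICC is 0-0.1. The figure for employment rests further on an assumed employment rate and share graduating, so it should be read as similar rather than established. The documents do not support saying that the protocol forbids a correction, or that the inflation from this source alone is large.

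**What to change.** In 20.11b and 20.11c, name bias-reduced cohort-robust standard errors (CR2, or an arm-level K/(K-1) factor) and a t reference on cohort-based degrees of freedom. Without quarter terms, 2K-2 serves the Sudbury contrast. If any quarter terms are kept, the degrees of freedom must be set for that model, and its error rate checked by simulation before the choice is final.

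An alternative is a cohort-level permutation test. It must re-randomise within the site-specific blocks of 4 in Section 16.1; shuffling freely within site does not match the allocation.

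The cost is wording and a change in the analysis code, with no new data. At 10 cohorts per arm the interval for ICM10 versus BCM widens by sqrt((10/9)/(40/39)) × 2.101/1.960 = 1.041 × 1.072 = 1.12, about 12%. The logit-scale test also becomes slightly conservative in some settings, at about 4%.
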